**Figure 6 F6:**
[figure not shown]
**A hypothetical sphere of a glomerulus**.

$${\text{A}}_{\text{h}}\times 2\text{h = }\int_{-\text{h}}^{\text{h}}\pi \left({\text{r}}^{2}\text{ - }\;{\text{x}}^{2}\right)\text{dx}$$

where A_h _is the average rea of the observed circle. Hence, A_h _is estimated by:

$${\text{A}}_{\text{h}}=\frac{1}{2\text{h}}\int_{-\text{h}}^{\text{h}}\pi \left({\text{r}}^{2}\text{ - }{\text{x}}^{2}\right)\text{dx = }\frac{\pi }{2\text{h}}{\left[{\text{r}}^{2}\text{x - }\frac{{\text{x}}^{\text{3}}}{3}\right]}_{-\text{h}}^{\text{h}}=\frac{\pi }{2\text{h}}\left(2r^{2}\text{h - }\frac{2}{3}{\text{h}}^{3}\right)=\pi \left({\text{r}}^{2}-\frac{{\text{h}}^{2}}{3}\right)$$

Using the Pythagorean theorem, $\text{h}=\sqrt{{\text{r}}^{2}-{\text{r}}_{\text{o}}{}^{2}}$

Where r is the glomerular radius and r_o _is the cut-off value of the observed glomerular radius (Figure 6).

Substituting h with a function of r and r_o _gives:

$${\text{A}}_{\text{h}}=\pi \left({\text{r}}^{2}-\frac{\left({\text{r}}^{\text{2}}-{\text{r}}_{\text{o}}^{2}\right)}{3}\right)=\pi \left(\frac{2}{3}{\text{r}}^{2}+\frac{1}{3}{\text{r}}_{\text{o}}^{2}\right)$$

A_cortex_s _(Area of the cortex of the section in a biopsied specimen) is calculated as:

$${\text{A}}_{\text{cortex\_s}}={\text{L}}_{\text{a + b}}\times {\text{d}}_{\text{b}}$$

Where d_b _is the internal diameter of the biopsy needle and L_a+b _is "a + b" in Figure 5 for the total cortex length in biopsied specimens.

VF _glom/cortex _(Volume fraction of glomeruli/cortex) is equal to AF_glom/cortex _(Area fraction of glomeruli/cortex on the section).

$$\text{V}{\text{F}}_{\text{glom}/\text{cortex}}=\text{A}{\text{F}}_{\text{glom}/\text{cortex}}=\frac{{\text{N}}_{\text{s}}\times {\text{A}}_{\text{h}}}{{\text{A}}_{\text{cortex - b}}}$$

Where N_s _is the number of observed glomeruli in a biopsied specimen.

Finally, the total number of glomeruli (N_total_) was calculated as:

$${\text{N}}_{\text{total}}\;=\;\frac{\text{Total}\;\text{glomerular}\;\text{volume}}{\text{one}\;\text{average}\;\text{glomerular}\;\text{volume}\;}\;=\;\frac{\text{V}{\text{F}}_{\text{glom/cortex}}\;\times \;{\text{V}}_{\text{Cortex}}}{\frac{4}{3}\;\pi {\text{r}}^{3}}$$

Where V_cortex _is the volume of the cortex estimated by MRI.

In this study, the value of r will be decided after calculating the means of approximately 5% of the attending patients by random sampling. Therefore, "r" is not a variable in the final calculation.

### Statistical analysis

All data are expressed as the means (SD). The primary parameter for assessment is the composite of the total mortality, renal death, cerebro-cardiovascular events, and a 50% reduction in the eGFR. We will use a Cox proportional hazard model for the analysis. We will check for confounders, interactions and multicollinearity among the independent variables. The final models will be adjusted by all significant variables, as well as confounders and other baseline covariables judged to have clinical importance. The secondary parameter is the rate of eGFR decline per year. A multivariate regression analysis will be used for the analysis. The significance level on both sides in the hypothesis testing will be set at 0.05. The analyses will be performed using the SPSS statistics software program version 19.0. (IBM Corp.)

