### Study design

In a multicenter, prospective (minimum 3 and maximum 5 years follow-up) study, approximately 600 patients with CKD who undergo a kidney biopsy for their diagnosis and will be enrolled from January 2011 to March 2013. These CKD patients will be recruited from 10 hospitals belonging to the National Hospital Organization of Japan. The hospitals participating in this study are spread throughout Japan (Hokkaido, Kanazawa, Chiba, Nagoya, Kyoto, Osaka, Fukuoka, and Nagasaki prefectures). This protocol was submitted to the UMIN-Clinical Trial Registration on January 1, 2011, and its unique trial number is UMIN000004784.

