### Clinical follow-up and data collection

Patients will continue to have medical consultations and will receive examinations and/or treatment as usual. We will not direct physicians to prescribe any preferred drug, examination, or to give any specific medical advice. We will also not ban the physicians from prescribing any particular drugs.

The data for patients will be collected once a year after the kidney biopsy, and will be followed until March 2016. We will permit the data collected during the antero-posterior three months of the day of the kidney biopsy to be analyzed as well. The data collection plan is shown in Figure 3.

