**Figure 3 F3:**
[figure not shown]
**Registration form to report follow-up data**. The original Japanese form was translated to English.

In this study, a cerebro-cardiovascular event was defined as an acute myocardial infarction, angina pectoris, and cerebro-vascular diseases. In addition, in order for a myocardial infarction to be reported in this study, it has to fulfill at least two of the following: (1) chest symptoms, (2) ECG changes, (3) elevated cardiac enzymes. Angina is defined as the presence of ECG abnormalities with chest symptoms and the need for catheter or surgical treatment. Furthermore, a cerebro-vascular event is defined as cases with neuropathy lasting more than 24 hours continuously and with proof of a causative lesion by CT scan or MRI (TIA and asymptomatic small infarction are not included). If no data is tracked during the follow-up, the reason will be recorded (stopped visiting the hospital, transferred to another hospital, moved to a new house, offered to stop the medical consultation, and so on).

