### Parameters for the assessment

The primary parameter that will be assessed is the composite of the total mortality, renal death (starting maintenance hemodialysis and peritoneal dialysis, kidney transplantation), cerebro-cardiovascular events (ischemic heart disease, cerebral hemorrhage, cerebral infarction), and a 50% reduction in the eGFR. The secondary parameter is the rate of eGFR decline per year.

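### The regression named for yearly eGFR decline makes no use of the repeated yearly values and no allowance for unequal follow-up, which mainly costs precision

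*Protocol article*

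**What the plan says.** The Parameters for the assessment section defines the endpoint: "The secondary parameter is the rate of eGFR decline per year". The Statistical analysis section gives the primary composite a specific model ("We will use a Cox proportional hazard model for the analysis") and the secondary parameter a general one: "A multivariate regression analysis will be used for the analysis".

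The data behind the rate are repeated and uneven in length:

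- Clinical follow-up and data collection: "The data for patients will be collected once a year after the kidney biopsy, and will be followed until March 2016".
- Study design: "In a multicenter, prospective (minimum 3 and maximum 5 years follow-up) study", with enrolment from January 2011 to March 2013.
- A series can also end early. The primary composite includes death and "renal death (starting maintenance hemodialysis and peritoneal dialysis, kidney transplantation". Stopped visits and transfers are foreseen ("If no data is tracked during the follow-up, the reason will be recorded"), and the sample-size rationale assumes 10% withdrawal.

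The article does not say how the rate is derived, whether each patient gives one value, whether values are weighted, or whether anyone is excluded.

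**The concern.** When the outcome is a rate and the method is a multivariate regression, the natural reading is two stages: compute one slope per patient, then regress the slopes on nephron number and baseline covariates. That discards how well each slope is known. A slope from a baseline and one yearly value would count as much as a slope from six values.

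At stake is the precision of the nephron-number effect on eGFR decline, the study's only stated secondary parameter. Follow-up is uneven by design, because everyone is followed to the same calendar date, so the issue arises even with no dropout.

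**Working it through.** **The plan's own figure.** There is none to reproduce. The sample-size rationale is for a log-rank test on the primary composite. No slope, SD or power is given for eGFR decline.

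**Step 1: error variance of a slope, from the visit schedule alone.** Take yearly visits including baseline, exact yearly spacing and a common residual variance σ². A least-squares slope then has error variance σ²/Sxx, where Sxx = Σ(t − mean t)².

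| Visits (years) | Values | Sxx | Error variance |
|---|---|---|---|
| 0-1 | 2 | 0.5 | 2.0 σ² |
| 0-3 | 4 | 5 | 0.2 σ² |
| 0-5 | 6 | 17.5 | 0.057 σ² |

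- 3-year against 5-year completer: 17.5/5 = 3.5.
- One-year series against 5-year completer: 17.5/0.5 = 35.
- One-year series against 3-year completer: 5/0.5 = 10.

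**Step 2: add true differences between patients.** In the second-stage regression a slope's total variance is τ² + σ²/Sxx, where τ is the between-patient slope SD. The article gives neither σ nor τ. Assume σ = 4 to 8 and τ = 2 to 4.

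- Mildest case, σ = 4, τ = 4: 16 + 16/5 = 19.2 at 3 years and 16 + 16/17.5 = 16.91 at 5 years, ratio 1.1. At one year, 16 + 16/0.5 = 48, ratio to 5 years 2.8.
- Strongest case, σ = 8, τ = 2: 4 + 64/5 = 16.8 at 3 years and 4 + 64/17.5 = 7.66 at 5 years, ratio 2.2. At one year, 4 + 64/0.5 = 132, ratio to 5 years about 17.

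Among completers the imbalance is therefore modest. Short series drive most of it.

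**Step 3: effect on the regression coefficient.** A simulation used residual SD 4-8, slope SD 2-4, 5% loss per year and eGFR values up to near-dialysis level (all assumed, 12 settings). Unweighted per-patient slopes had 1.09 to 1.65 times the variance of a random-slope model. In standard-error terms that is √1.09 = 1.04 to √1.65 = 1.28. Put another way, the unweighted analysis is as precise as the mixed model would be on 1/1.65 = 61% to 1/1.09 = 92% of the patients. The mixed model had the lower root mean square error in all 12 settings, with at most about 4% attenuation.

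**Step 4: sensitivity to truncation.** A second simulation assumed 600 patients, 3 to 5 years, no random loss, mean slope −3 per year, residual SD 4 or 8, slope SD 2 to 6 and a true coefficient of 1.0.

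| eGFR series used | Per-patient slopes | Random-slope model | Patients with no slope |
|---|---|---|---|
| Until dialysis level | 0.97-1.02 | 0.95-1.01 | 0.03-0.5% |
| Also stopped before a 50% fall | 0.92-0.98 | 0.85-0.95 | 0.3-2.9% |

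Across both rows the mixed model's SD was 1% to 25% smaller. In the first row the variance ratio ran from (0.090/0.089)² = 1.02 to (0.283/0.238)² = 1.41. With no random loss and small residual error the gain can therefore be close to nil.

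**The case against.** **The reading is inferred.** The article does not say ordinary least squares, one rate per patient or equal weights. Slope derivation and weighting are often left to a full protocol or SAP that is not shown. This stands as a limit on wording. It does not remove the point, because the section names a class of analysis for this endpoint. A later plan with a repeated-measures model would have to replace or reinterpret that sentence.

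**The stronger reading fails.** A reader might infer that the plan drops the fastest progressors and so biases the result. No exclusion rule is stated. Even on the two-stage reading, only a patient with no post-baseline eGFR lacks a slope; one who reaches dialysis after the first yearly value still has one. A simulated cohort of 540 (600 less 10%) with 5% loss per year had about 28 patients without a slope, but loss alone predicts 540 × 0.05 = 27. With no random loss, the share was at most 2.9%. Those few did decline faster than average (mean −4 to −21 per year against −3 overall), yet per-patient slopes were not materially biased when values ran to dialysis level. The article also expects few stage 4 or 5 patients, and deaths, renal deaths and 50% falls count in the primary composite.

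**The remedy is imperfect.** A mixed model shrinks short, steep series and does not cure informative truncation. When series stopped before a 50% fall it was the more attenuated method. This stands and shapes the fix.

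**The 35-fold ratio flatters the case.** It counts measurement error only and applies only to one-year series. The coefficient-level figure is the one to rely on.

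**Conclusion.** The point holds as a matter of efficiency. The named analysis, read naturally, gives equal weight to slopes whose error variances differ 3.5-fold between 3- and 5-year completers and up to 35-fold for a one-year series. Those ratios rest only on the yearly schedule and a common residual variance. The cost to the coefficient, about 1.1 to 1.65 times the variance of a random-slope model, rests on assumed SDs and 5% loss per year, none of which the article gives. With little loss and small residual error it shrinks towards nothing. The change is worth making because a better method exists for the same data. It concerns a secondary parameter and leaves the primary Cox analysis untouched.

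**What to change.** Replace the Statistical analysis sentence on the secondary parameter with text to this effect: all yearly eGFR values, from baseline up to dialysis or transplantation, will be analysed in a linear mixed model with random intercept and slope. The test is the nephron number by time interaction, adjusted for the same baseline covariates and their time interactions. Patients with any eGFR value are included.

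State that values after a 50% fall stay in the series until dialysis or transplantation, since stopping them earlier is what attenuated the mixed model most.

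Add one sensitivity analysis for series that end because of fast decline: a joint slope-and-event model, or the per-patient-slope regression. Agreement between it and the mixed model would indicate that truncation matters little.

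The cost is a few sentences. The mixed model runs in standard software, and no new data or visits are needed. The joint model takes more programming; the per-patient-slope regression takes almost none.

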### Sub-cohort study to establish an equation for the renal cortex volume

Some of the participating patients will undergo MRI to measure the cortex volume of their kidney, because MRI is the safest procedure and has highest resolution to separate the cortex from the medulla, as reported in other studies [16,17]. However, it is unrealistic to perform MRI for all CKD patients because of its high cost. Therefore, we will attempt to establish the equation to calculate an approximate value of the kidney cortex volume measured by MRI.

### Measurement of the cortex volume by MRI

While MR imaging sometimes does not provide sufficient contrast for the soft tissues, in many cases, it is possible to distinguish the cortex and the pith of the kidney by tomography. Therefore, we will image the entire kidney with axial MRI, and calculate the renal cortical volume by multiplying the slice thickness and the slice number of the kidney which we measured on each axis tomogram. For this purpose, we found that an MR image that provided the best contrast between the cortex and medulla of the kidney was obtained using the following sequence: 2D Turbo FLASH TR = 1570 ms, TE = 2.74 ms, TI = 1000 ms, Flip Angle = 15°, Fat sat (-). We will manually draw the ROI in the kidney, and the regional choice in the axial image of the kidney will be determined by specialized radiological technologists (with AZE virtual Place FUJIN workstation, AZE Co. Ltd., Tokyo).

The calculations used for the renal cortical and whole kidney volume are as follows:

Wholekidneyvolume= ∑Areaofthekidneyineachslice×slicethickness(sliceinterval)

Renalcortexvolume= ∑Areaofthecortexineachslice×slicethickness(sliceinterval)

## Discussion

Chronic kidney disease is regarded as public health problem throughout the world [4]. In this study, we will mostly focus on the importance of the nephron number as a predictor of the outcome of CKD patients. The nephron numbers vary widely among individuals [25,26]. One report described that the range is from 227,327 to 1,825,380 per kidney, which is an 8-fold difference [12]. Compensatory adaptation to a reduced nephron number results in an increased single nephron GFR and hyperfiltration. This mechanism was described as the hyperfiltration theory by BM Brenner [14,27]. In fact, it was shown that nephron number is associated with the progression of CKD [25]. Furthermore, many reports indicate that low birth weight is a risk factor for the progression of CKD [6-9,13], which further emphasizes the importance of the nephron number, because the nephron number is positively correlated with the birth weight [11,12]. Therefore, we hypothesized that the individual nephron number would be useful for predicting the outcome of CKD.

As mentioned above, although it is likely that estimating the nephron number will be useful to predict the outcomes of CKD patients, it is currently not possible to determine the nephron number in living subjects. It was reported that the glomerular density is correlated with the prognosis of IgA nephropathy [28]. Although the glomerular density probably correlates with the nephron number, the individual renal cortex volume should largely affect the nephron number. In addition, all of the previous clinical studies concerned with birth weight or nephron number were retrospective. The purpose of this study is to examine whether the estimated nephron number can predict the outcome of CKD patients. It will be the first prospective study of this type ever to be performed.

For this purpose, 3 obstacles will have to be overcome. First, it is not possible to measure the renal cortex volume in the normal clinical setting. To develop a method for estimating this parameter, a one sub-cohort study is being performed. MRI can differentiate the cortex from the medulla because of its high resolution. Other studies also evaluated the total nephron number of dog kidneys or human donor kidneys by the cortex volume measured by MRI [16,17]. However, we cannot perform MRI for all CKD patients because it is too expensive and not always available. For this purpose, we will first accurately measure the renal cortex volume of some of the participating patients by MRI. Next, we will establish a method to calculate an approximate value of the renal cortex volume measured by MRI. The estimating equation may consist of the kidney size measured by ultrasound, patient sex, eGFR, birth weight, present body weight, and so on. This sub-cohort study will provide us with a method for determining the cortex volume in the general clinical setting. As a second step, we will need to estimate the nephron number while the subjects are still alive. Although measurements of the cortical glomerular volume fraction and mean glomerular volume in individuals are most accurate for calculating the glomerular density, such analyses are unfortunately very time-consuming and therefore a difficult to routinely perform in general clinical situations. Therefore, in this study, the total nephron number will be estimated by performing simpler analyses of biopsied specimens as described above. As the final step, the capacity of the estimated nephron number to predict the outcome of CKD patients will be assessed. The primary parameter for assessment is a composite of the total mortality, renal death, cerebro-cardiovascular events, and 50% reduction in the eGFR. The secondary parameter is the rate of eGFR decline per year. All of these parameters affect the quality of life and survival of CKD patients.

In this study, we aim to establish a method to predict the outcome of CKD patients at the time of their kidney biopsy. Therefore, the data collected during the follow-up period will be restricted (Figure 3). Because body weight may affect the serum creatinine level, we will include this data. There is a possibility that we may also analyze the impact of the urinary protein level and usage of renin-angiotensin-aldosterone system blockers, because both are major effectors of the prognosis of CKD patients [29-31]. Therefore, these data will also be collected. On the other hand, we also require a lot of data at enrollment (Figure 2), all of which will be variables of the equation used to calculate the renal cortex volume or predict the CKD outcomes. We plan to develop an equation that can be used for all CKD patients. However, nephrologists will likely need different equations for each disease, for example, diabetic nephropathy, benign nephrosclerosis, and IgA nephropathy. Therefore, we will further analyze the data by individual diseases.

This study includes the first trials to estimate the renal cortex volume and nephron number in the general clinical setting. In addition, this study is the first prospective study to examine whether the nephron number can predict the outcome of CKD patients. The results from this study should provide powerful new tools for nephrologists in routine clinical practice.

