## Methods and Design

### Hypothesis

The nephron number, which is estimated from the glomerular density in kidney biopsy specimens and the volume of the renal cortex, can predict the outcome of a CKD patient (Figure 1).

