### Rationale for the number of patients

This study aims to predict the outcome of chronic kidney disease using the estimated nephron number. We assumed that the time from entry to event will be independently and exponentially distributed. The planned sample size was based on a two-tailed log-rank test with the significance level set to 0.05, and the power level set at 0.80. The ratio of low birth weight infants per total newborns in Japan was reported to be 0.086 in 1960 and 0.097 in 2007. During this period, the rate has been consistently increasing http://www.mhlw.go.jp/english/database/db-hw/vs01.html. The rate of LBW may be higher in the CKD patients than in normal subjects. We assumed that the rate of LBW would be 0.095 in the CKD patients in this study. This study is planned with an accrual interval of 2 years, and additional follow-up after the accrual interval of 3 years. The event rates were assumed to be 0.1 in the normal birth weight group and 0.2 in the low birth weight group by several studies [8,20,21]. The required sample size was therefore calculated to be 50 for the low birth weight group and 476 for the normal birth weight group [22]. Assuming that 10% of subjects would withdraw, we used the simple number of 600 as the target number of patients to recruit for this study.

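### The aim is to assess how well nephron number predicts outcome, but the stated analysis yields only tests of association, with covariates chosen partly by significance

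*Protocol article*

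**What the plan says.** The Hypothesis section states that estimated nephron number can predict a CKD patient's outcome. The Discussion describes three steps and ends: "As the final step, the capacity of the estimated nephron number to predict the outcome of CKD patients will be assessed". It then names a product: "We plan to develop an equation that can be used for all CKD patients", with further analyses by individual disease.

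The Statistical analysis section says of the primary composite: "We will use a Cox proportional hazard model for the analysis". Of the covariates it says: "The final models will be adjusted by all significant variables, as well as confounders and other baseline covariables judged to have clinical importance". For yearly eGFR decline it says: "A multivariate regression analysis will be used for the analysis". The level is given once for all: "The significance level on both sides in the hypothesis testing will be set at 0.05". The Rationale for the number of patients is also built on a significance test, a "two-tailed log-rank test with the significance level set to 0.05, and the power level set at 0.80", comparing low with normal birth weight.

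The article names no C-index or other discrimination measure, no calibration, no correction for optimism and no validation sample. The Discussion lists eGFR among the variables that may enter the equation for cortex volume. In the section on estimating the total nephron number, cortex volume is a direct multiplier of that number.

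**The concern.** A significant adjusted hazard ratio shows that a marker is associated with outcome. It does not show how well the marker separates patients who will have an event from those who will not, or whether predicted risks are right. With a moderate number of events, a weak marker can be clearly significant.

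Two features make this matter more here. First, estimated nephron number may carry eGFR inside it through the cortex-volume equation. If baseline eGFR is not certain to be in the outcome model, a significant coefficient may partly restate what the clinician already knows. Second, some covariates are kept because they are significant in these data. Performance measured on the patients used to choose the model then tends to look too good. At stake is whether the results can support the article's claim of a useful tool for routine practice.

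**Working it through.** **1. Reproduce the plan's sample size.** Inputs, all from the Rationale for the number of patients: event rates 0.1 and 0.2 (no time unit given), low-birth-weight share 0.095, accrual 2 years, further follow-up 3 years, two-sided 0.05, power 0.80.

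Read the rates as yearly probabilities: λ₁ = −ln 0.9 = 0.1054, λ₂ = −ln 0.8 = 0.2231, hazard ratio 2.12.

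Probability of an event by study end: P(λ) = 1 − (e^(−3λ) − e^(−5λ)) / (2λ). This gives P₁ = 0.343 and P₂ = 0.587.

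N = (1.960 + 0.842)² × [λ₂²/(0.095 P₂) + λ₁²/(0.905 P₁)] / (λ₂ − λ₁)² = 7.849 × 0.9287 / 0.01387 = 525.4.

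Split: 49.9 and 475.5, that is 50 + 476, exactly as stated. The sample-size arithmetic is not in question, and the yearly reading is the one that fits it.

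**2. Expected events.** 600 less 10% leaves 540 patients. Overall event probability = 0.095 × 0.587 + 0.905 × 0.343 = 0.366, so 540 × 0.366 ≈ 198 events.

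**3. From events to hazard ratio and C-index.** Assume nephron number is roughly normal after any transformation; the documents give neither its SD nor a hazard ratio for it. For a coefficient b per SD:
- just significant: b = 1.960/√198;
- detectable with 80% power: b = 2.802/√198;
- the same, if other covariates explain a share R² of the marker: b = 2.802/√(198 × (1 − R²)).

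Concordance is C = E[1/(1 + e^(−b|d|))], with d the difference between two patients, distributed N(0, 2).

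| Case | b | HR per SD | C |
|---|---|---|---|
| Just significant | 0.139 | 1.15 | 0.54 |
| 80% power | 0.199 | 1.22 | 0.555 |
| 80% power, R² = 0.3 (assumed) | 0.238 | 1.27 | 0.566 |

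Chance is 0.50. Simulation with the same accrual and follow-up gave a Harrell C of 0.540 for the first case.

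**4. Two comparisons.** The design effect itself, hazard ratio 2.12 in 9.5% of patients, gives C = 2 × 0.095 × 0.905 × 2.12/3.12 + 0.5 × (0.095² + 0.905²) ≈ 0.53. For the secondary regression with n = 540, p = 0.05 is reached at a partial R² of about 1.96²/(1.96² + 538) = 0.007.

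**5. Sensitivity.** If 0.1 and 0.2 were 5-year risks, the event probabilities would be 0.081 and 0.163, giving 540 × 0.0886 ≈ 48 events. Just significant would then be a hazard ratio of about 1.33 (C about 0.58), and 80% power about 1.50 (C about 0.61). That reading requires about 1,903 patients, so it does not match the stated size.

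**The case against.** The strongest reply is that this is a condensed article. A full protocol or analysis plan may name performance measures, and their absence here is not itself an error. That stands. The point rests instead on what the article does fix: a set of association tests, with covariates chosen partly by significance, set against an aim of assessing predictive capacity.

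Several stronger readings are tempting, and the documents do not support them.
- A reader might infer that the plan will call any p below 0.05 a successful predictor. The article never says so; it simply gives no other criterion.
- A reader might infer that the study cannot answer its own question because it does not measure gain over routine variables. Its literal question is whether nephron number can predict outcome. Added value is a sensible sharpening of that, not the article's wording.
- A reader might infer that the resulting tool would barely discriminate. The C values above are for nephron number alone, at the smallest effects of interest. The planned equation would draw on many enrolment variables, and its C-index cannot be computed from the documents.
- A reader might infer that the equation will be judged on its own development data without correction. The article does not describe how it will be judged.

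It is also fair to say that testing nephron number in an adjusted Cox model is close to a likelihood-ratio test of adding it to the same covariates. Clinically important covariates are allowed for, so eGFR and urinary protein may well be included. What is lacking is a fixed comparator that guarantees them, and a measure of performance.

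**Conclusion.** The concern holds as a mismatch between the predictive aim and the stated analysis. Significance at 0.05 is compatible with a marker-alone C-index of about 0.54, and the effect detectable with 80% power with about 0.555 to 0.57. A significant coefficient would therefore say little about predictive capacity. The figures rest on yearly event rates, 10% loss, a roughly normal marker and, for the upper value only, an assumed R² of 0.3. They are threshold effects, not forecasts of what the study will find. The possible route of eGFR into nephron number makes a fixed clinical comparator more than a matter of style. This is a worthwhile and cheap improvement; it does not invalidate the design.

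**What to change.** In Statistical analysis, replace significance-based covariate selection with a prespecified clinical Cox model, for example age, sex, baseline eGFR, urinary protein and diagnosis. Then:
- test nephron number added to that model;
- report the change in C-index with a confidence interval, and calibration at 3 years, the minimum follow-up;
- correct both for optimism by a bootstrap that repeats the modelling steps;
- word any claim of predictive value according to the gain over the clinical model;
- label the disease-specific equations as exploratory.

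The cost is analysis work on data already being collected. The reported performance will be less flattering.
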